##### Utility measures

The primary utility measure of the study is quality adjusted life years (QALYs), and will be calculated from the SF-12 scores (scale 0-100; lower score indicates poorer quality of life) [32].

##### Other variables

The main independent variable is the intervention arm: MBEGI, or usual clinical care.

Sociodemographic and clinical variables were detailed in the study protocol [21]. Among others, clinical variables are PHCC and hospital emergency visits due to current sub-acute LBP episode; patient compliance with recommendations and treatments; prescribed diagnostic tests; prescribed pharmacological treatment; referrals to other departments; and nonpharmacological treatment measures [41]. Absenteeism will be calculated, and reduced work productivity (presenteeism) will be measured by the Quantity and Quality instrument (QQ). The amount and quality of productivity will be measured on a 10-point numerical rating scale, with 0 representing "nothing" and "very poor quality," respectively, and 10 representing "normal quantity" and "normal quality," respectively [42,43].

##### Other non-pharmacological therapeutic measures and Patient Compliance

The non-pharmacological therapeutic measures are detailed in Table 4.

**Table 4 T4:** Measurements of cost

Measurements of costs					
**Type of cost**	**Costs for**	**Specification**	**Source of resources used**	**Source of costs per 'unit'**	**Cost calculation**

Medical direct costs	Primary Health Care consultations	General Practitioner Practice nurse Physiotherapist Psychologists	Self-reported and comparison the answers by E-cap (electronical clinical records e-cap)	Catalan Institute of Health provider	Number of visits × tariff
	
	Secondary care consultations	Other specialists	Self-reported and comparison by E-cap	Catalan Institute of Health provider	Number of visits × tariff
	
	diagnostic tests	Radiology, magnetic resonance, scanner, electromyogram	Self-reported and comparison by E-cap	Catalan Institute of Health provider	Tests done × tariff
	
	Pharmaceutical treatment	muscle relaxants, analgesics, NSAIDs, corticoids, anxiolytic, Antidepressants and gastric protectors	Self-reported and comparison by E-cap	Standard Pharmaceutical Prices by Consejo General de Colegios Oficiales de Farmacéuticos	Medicines bought × price medicine
	
	Additional medical services	Traumatology, rehabilitation, neurosurgery, other therapies	Self-reported and comparison by E-cap	Catalan Institute of Health provider	Services provided × tariff
	
	Material provided in intervention	leaflet, booklet, CD, DVD	Provider	Provider; production costs	Number of material × price per material
	
	Material used in intervention	mat, postural stool, tennis ball	Provider	Provider; market price	Number of material × price per material

Non medical direct costs	Aid to patients who face disabilities	Aid in household, aid for young children	Self-reported	Patient	hours of aid × price per aid
	
	Additional therapies	Gymnasium, swimming, Yoga/Tai Chi/stretching, other	Self-reported	Patient	Number of months × price per month
		
		Acupuncture, osteopathy, massage, homeopathy, other therapies	Self-reported	Patient	Number of sessions × price per session

Indirect costs	Cost of lost productivity	Absenteeism	Self-reported and comparison by E-cap	Self-reported, profession classification assigned according to Spanish National Institute of Statistics	Days of work sick leave × salary

		Presenteeism	Self-reported	Self-reported, profession classification assigned according to Spanish National Institute of Statistics	reduction percentage × productivity

During follow-up visits (at 3, 6 and 12 months) we will ask the patient about compliance with treatment recommendations and data collection questionnaires will be completed.

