### Randomisation

In this study a cluster design is used because the intervention is delivered to groups. To minimise contamination, the unit of randomisation will be the PHCC. Those PHCCs who agree to participate will be randomly allocated to control or intervention groups by a random sequence generated by a computer programme in blocks of random size and prepared before recruitment of the PHCC by an independent statistician who will be blinded to the PHCC identity. The blocking factor was a randomly selected even number (i.e., 4, 6, or 8) and will vary as the recruitment continues. GP or nurses will be informed about their allocation after giving final consent to participation.

To minimise imbalance across intervention groups, randomisation was stratified by percentage of immigrants from developing countries registered in each district. We consider two strata, less than and more than 15% immigrants. This variable is taken as a proxy of socioeconomic level.

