##### Data collection and information sources

All participants will be invited to attend the PHCC for outcome assessments. They will be assessed at the first visit to the PHCC and at 3 months, 6 months, and 12 months after the onset of LBP. Primary data will be collected from the patient by an interview and the electronic clinical records. All outcomes will be measured at the individual level.

The data source of the costs of lost productivity and indirect costs of wages lost to LBP, whether remunerated or not, will be Spain's National Statistics Institute (INE) [44-46], calculated on the basis of the national classification of economic activity [45]. Each participant's profession will be placed into one of the categories of economic activity.

A human capital focus will be used to determine the cost of absenteeism from paid employment. This measure considers the social value of an individual to equal future potential production, measured by the value of anticipated lifetime income. A limitation of this method is it does not take unemployment into account (retirees or those with a disability), although we will correct for this by assigning a value equal to the minimum wage or average salary of their profession [46,47].

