To adjust comparisons and to account for cluster randomisation, multilevel linear regression analyses on repeated measures on each of the outcome scales will be used to assess the effect of intervention and to investigate the factors that influence each of the outcome scales at each time point. The possible association between intervention and time will be studied. The PHCC and the individual will be considered as random effects and intervention and time as fixed effects.

The incremental cost-effectiveness ratios were calculated as the difference in mean costs between the MBEGI and the usual care divided by the difference in mean effect, measured in natural unit, between MBEGI and the usual care.

Utilities will be calculated from the SF-12 scores with the corresponding Oxford University algorithm. The QALY will be calculated using these utilities, adjusted by time. The incremental cost-utility ratio will be calculated by dividing the difference in mean total costs between the MBEGI and the usual care by the difference in QALYs [56,57].

To determine the uncertainty surrounding these ratios, 95% confidence intervals for cost-effectiveness ratios will be calculated by the non-parametric bootstrap method [51].

Acceptability curves will be use to determine the probability that the MBEGI will be cost effective compared with usual clinical care at different values of the maximum acceptable ratio.

A deterministic sensitivity analysis will be performed to assess the robustness of the results [58]. The sickness days, GP visits and the number of medications will be measured to assess the impact on costs and cost-effectiveness. The discount rate will be 1% and 5%.

Confidence intervals around point estimates will be reported. The results will be presented in a disaggregated as well as aggregated form.

The significance level of all models will be set at 5%. The SPSS statistical package for Windows, version 19 (SPSS Inc., Chicago, IL) and the Stata/SE version 11·1 for Windows (StataCorp LP) will be used for statistical analysis.

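### Lost work is priced at each patient's occupational salary while the incremental cost is an unadjusted difference in means, so a difference in job mix between arms enters the ICER and ICUR

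*Protocol article*

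**What the plan says.** Table 4 of the protocol article gives the absenteeism cost as "Days of work sick leave × salary". Its price source is "Self-reported, profession classification assigned according to Spanish National Institute of Statistics", and the presenteeism row cites the same source. The section on data collection and information sources adds: "Each participant's profession will be placed into one of the categories of economic activity". It also states: "A human capital focus will be used to determine the cost of absenteeism from paid employment". For people outside paid work the plan corrects by "assigning a value equal to the minimum wage or average salary of their profession". Visits, tests and drugs, by contrast, carry one tariff or list price for everyone.

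Under Statistical Analysis, the cost-effectiveness ratio is defined as a difference in arm mean costs over a difference in mean effect. The cost-utility ratio "will be calculated by dividing the difference in mean total costs between the MBEGI and the usual care by the difference in QALYs". The multilevel regression with centre and individual as random effects is stated for the outcome scales; costs are not named there. The sensitivity analysis lists sickness days, GP visits, number of medications and the discount rate, but not the wage.

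Under Randomisation, centres are stratified into two levels of district immigrant percentage: "This variable is taken as a proxy of socioeconomic level".

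**The concern.** A patient's occupational wage is fixed before entry and the intervention cannot change it. Because it multiplies days lost, the arm difference in absenteeism cost mixes two things: the difference in days, which the intervention may affect, and the difference in job mix, which it cannot. No stated step separates them. The Discussion expects most of the cost of low back pain to be indirect, so this is likely to be the largest cost item.

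Only 38 centres are randomised. The plan treats socioeconomic level as worth balancing, but controls it with a two-level district proxy. The Discussion assumes similar unemployment in the two groups and says nothing about wage level. Part of a reported saving, or the lack of one, could therefore reflect which occupations each arm recruited.

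**Working it through.** **The plan's own figure first.** Sample size inputs: difference 2.5, SD 5.7, alpha 0.05 (two-sided assumed), power 90%, ICC 0.1, 25 per centre, 20% dropout.
- Per arm without clustering: 2 × (1.96 + 1.2816)² × 5.7² / 2.5² = 109.24, rounded up to 110.
- Design effect: 1 + 24 × 0.1 = 3.4.
- Per arm: 109.24 × 3.4 / 0.8 = 464.3, or 110 × 3.4 / 0.8 = 467.5. The total is 929 to 935, against 932 stated. It reproduces.
- 932 / 25 = 37.3, hence 38 centres, with 466 / 19 = 24.5 patients each.

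**Euros per 1% wage difference.** The Background gives 21.9 days per episode and 1260 € per worker per year. If the two share a base, the daily price is 1260 / 21.9 = 57.5 €. With 21.9 days in both arms, a 1% difference in mean wage gives 0.01 × 1260 = 12.6 € per patient; 5% gives 63 €, 10% gives 126 € and 20% gives 252 €. At one common wage the difference is 0.

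**How large chance imbalance could be.** Wage CV and wage ICC are not in the article and are assumed. Relative SE of the arm difference in mean wage = CV × √(2 × DE / 466), with DE = 1 + (24.5 − 1) × ICC.

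| Wage CV | Wage ICC | DE | Relative SE | 95% range | € per patient | Equivalent days |
|---|---|---|---|---|---|---|
| 0.3 | 0.05 | 2.18 | 2.9% | ±5.7% | ±72 | 1.2 |
| 0.5 | 0.10 | 3.35 | 6.0% | ±11.8% | ±148 | 2.6 |

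Over wage CV 0.3 to 0.5 and ICC 0.02 to 0.20, the range runs from ±4.7% (±59 €) to ±15.3% (±193 €).

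**Set against the noise in days alone.** With an assumed days CV of 2 and a common wage, the 95% range is 1.96 × 1260 × 2 × √(2 / 466) = ±324 €. With design effects 2.18 and 3.35 it is ±478 € and ±592 €. The wage component is real but the smaller part.

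**Effect on precision.** If wage and days are independent, the squared CV of cost is CVd² + CVw² + CVd² × CVw². With CVd = 2:
- CVw = 0.3: √4.45 / 2 = 1.05.
- CVw = 0.5: √5.25 / 2 = 1.15.

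A simulation with no intervention effect, 19 centres of 25 per arm and log-normal wages and days gave these ratios of SE, own wage over common wage:

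| Log-scale wage–days correlation | SE ratio |
|---|---|
| +0.3 | 1.28 to 1.70 |
| 0 | 1.05 to 1.23 |
| −0.3 | 0.82 to 0.90 |

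The ratio passes 1 at a correlation of roughly −0.05 to −0.12. The mean simulated cost difference was about 0 in every setting, as expected under randomisation.

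**Effect of the fix.** In simulation, adjusting the cost difference for entry wage cut the SE by about 0 to 16% over the settings tried and did not materially raise it. With wage and days unrelated, it removed the spurious difference of roughly 120 € produced by a 10% wage shift. Replacing own wage by a common wage instead raised the SE from 168 to 202 € in one setting with correlation −0.3.

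**The case against.** Pricing by occupation is not an error. It follows from the societal perspective, bottom-up costing and human-capital approach that the plan adopts. A common wage answers a somewhat different question, because it drops any link between who is helped and what their output is worth. That stands, and it is why the base case should not be replaced.

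Randomisation makes job-mix imbalance a matter of chance, stratification removes part of it, and the interval exists to cover the rest. That also stands. A reader might infer that the plan builds in a bias or necessarily widens its intervals. The article supports neither: the expected imbalance under randomisation is zero, and the effect on width changes sign if lower-paid workers take clearly more sick leave.

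The plan reports days off work and resource use by arm and presents disaggregated results, so equal days with unequal costs would be visible. Visibility, however, does not correct the ratio or the acceptability curve. The plan also commits in general terms to individual-level regression that respects clustering, and details may sit in documents not shown. Yet the article itself fixes the ratios as plain mean differences and names only outcome scales for adjustment.

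On recruitment, the Blinding section says consent precedes allocation. But allocation follows the centre, GPs and nurses know it and identify the patients, and intervention sessions take 2 × 4 + 2 = 10 hours. Selection by occupation is possible; nothing in the article shows that it occurs.

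**Conclusion.** The point holds in a limited form. A pre-entry characteristic enters what is likely to be the largest cost item with no stated adjustment, and no wage variant is named in the sensitivity analysis. The size is 12.6 € per patient per 1% difference in mean wage. That rests on 1260 € and 21.9 days sharing a base, although one is per year and the other per episode, and on both applying to every patient, although some may take no leave. The chance range of about ±59 to ±193 € rests wholly on assumed wage spread and clustering; if category averages are used as prices, the spread would be narrower. Presenteeism is included only because it cites the same price source, since its formula is worded differently. Bias arises only if recruitment after allocation differs by occupation. No figure for total cost, ICER or ICUR can be derived from the article.

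**What to change.** Keep own-profession salary as the base-case price. In the Statistical Analysis section, where the ratios are defined, state that the incremental cost is estimated from a model clustered by centre, with the patient's daily wage (or occupation category) at entry as a covariate. Use the adjusted difference in the ICER, the ICUR, their bootstrap intervals and the acceptability curves. For patients outside paid work, the covariate should be the same wage value that the costing assigns to them. Fix it at entry, so that later job changes cannot affect it.

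Add one item to the sensitivity analysis: absenteeism and presenteeism priced at one common daily wage in both arms. Comparing that run with the base case shows how far a saving comes from fewer lost days and how far from different jobs.

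The cost is analysis wording and one extra run, since profession is already collected. The adjustment removes imbalance fully only if the relation between cost and entry wage is similar in the two arms and adequately modelled; occupation categories are safer than a straight line if that is in doubt.

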##### Measures of resources and costs

The costs analysis will be conducted using a bottom-up approach (bottom-individual; up-societal costs). Average costs will be calculated for each particular type of cost. Costs related to both the MBEGI and the usual care will be collected. The costs of non-specific sub-acute LBP and its treatment consist of direct medical costs and direct and indirect non-medical costs [44]. An overview of the measured costs and the corresponding sources can be found in table 4.

Direct medical costs include those attributable to health care visits for the treatment of LBP: the cost of MBEGI material utilized and distributed to the patients; visits to primary care professionals, to other specialists, and to rehabilitation services; number of complementary tests; and costs of pharmacological treatment and disposable supplies for medical and emergency services use.

These costs will be assessed in accordance with the official rates most recently published in the *Diari Oficial de la Generalitat de Catalunya *(DOGC) for the public health service.

Direct non-medical costs will include home help received as a result of disability related to LBP, patient time directly related to the intervention (time spent in transportation, waiting rooms, and the intervention), non-medical activities (gymnasium, swimming, Yoga/Tai Chi/stretching), and additional therapies (acupuncture, osteopathy, massage, homeopathy).

Indirect non-medical costs include loss of productivity and will be calculated on the basis of time off work (absenteeism) as well as reduced productivity at the workplace (presenteeism). The respondent will be asked to quantify how much work was actually performed during regular hours and the quality of this work as compared with a normal work day [42,43].

Costs will be calculated in euros (€) based on the most actualized prices using the general Spanish consumer price index.

##### Data collection and information sources

All participants will be invited to attend the PHCC for outcome assessments. They will be assessed at the first visit to the PHCC and at 3 months, 6 months, and 12 months after the onset of LBP. Primary data will be collected from the patient by an interview and the electronic clinical records. All outcomes will be measured at the individual level.

The data source of the costs of lost productivity and indirect costs of wages lost to LBP, whether remunerated or not, will be Spain's National Statistics Institute (INE) [44-46], calculated on the basis of the national classification of economic activity [45]. Each participant's profession will be placed into one of the categories of economic activity.

A human capital focus will be used to determine the cost of absenteeism from paid employment. This measure considers the social value of an individual to equal future potential production, measured by the value of anticipated lifetime income. A limitation of this method is it does not take unemployment into account (retirees or those with a disability), although we will correct for this by assigning a value equal to the minimum wage or average salary of their profession [46,47].

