### Study population

Eligible patients will be identified by the GP or nurses when they consult for a new episode of sub-acute LBP or from searches of electronic clinical records. Patients are informed about the study objectives and those who agree to participate will be given written informed consent to sign.

Patients will be included if the current episode of LBP occurs suddenly after at least 6 months without LBP and lasts between 15 days and 12 weeks [24], and if they do not fulfil any of the exclusion criteria [20].

Furthermore, patients must be between 18 and 65 years old, understand Catalan or Spanish, and be available to participate for at least 12 months. Patients will be excluded if: (a) they are unwilling to participate in the multidisciplinary intervention trial; (b) LBP coexists with cognitive impairment, severe psychiatric disorders such as psychosis, or severe major depression; (c) any other cause of disability impedes answering the various questionnaires; (d) they are pregnant or breast-feeding; (e) they might have anti-inflammatory intolerance or allergy; (f) treatment has been received for physical problems in the preceding 3 months; (g) they have been referred for intensive functional restoration programmes; or (h) they have a confirmed diagnosis of fibromyalgia.

Furthermore, the GP has to ensure that the patient has no red flag signs or symptoms that are frequently associated with specific LBP or potentially severe illnesses [25-28].

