### Intervention group

In addition to the same individual intervention as the control group, patients allocated to the intervention group will receive an educational booklet "The Back Manual" [29] (a transculturally adapted Spanish version of the Back Book) [30] and a biopsychosocial multidisciplinary group intervention.

The group intervention will be carried out by a GP, a nurse, a psychologist and a physiotherapist. The programme consists of 2 sessions of 4 hours duration each and 1 session of 2 hours duration. Each group includes up to 12 participants. Details of the MBEGI intervention and the educational digital video disc (DVD) are included in Tables 2 and 3.

**Table 2 T2:** Components of the biopsychosocial multidisciplinary group intervention

GP + Nurse 2 hours	Objective: Resolve doubts, demystify concepts about LBP and promote adherence to the intervention
	■ Basics on anatomy and biomechanics of the spine
	■ Pain mechanisms
Theory program	■ Causes of pain and predisposing factors
	■ Type of pain, mechanical, inflammatory, and severity
	■ Healthy life habits

Practical program	■ Discuss with the participants the doubts, beliefs and myths about back pain and give positive messages

**Physiotherapist** **4 hours**	**Objective: Provide tools on exercises/postures to avoid the pain and the chronic course and improve quality of life**.

	■ Body posture and its implication in pain
Theory program	■ Ergonomics
	■ Benefits of relative rest

	■ Diaphragmatic breathing exercises as the basis for relaxation, body awareness and postural control.
	■ Pelvic floor/gyration exercises.
Practical program	■ Propioceptive and posture awareness exercises.
	■ Strengthening exercises of the psoas and the posterior chain: Paravertebral muscles, gluteus, ischiotibial muscles.
	■ Strengthening exercises of abdominal muscles, specially the abdominal transversus, gluteus, spinal extensors and scapular muscles.

**Psychologist** **4 hours**	**Objective: Provide participants with cognitive-behavioural therapy techniques**

Theory program	■ Influences of cognitions, emotions and behaviour in pain

	■ Relaxation guidelines and methods
	■ Cognitive restructuring (Modulation of negative thoughts affecting emotions and pain)
	■ Use of attention (Increasing attention focus)
Practical program	■ Assertiveness (improving social relationships)
	■ Problem solving (training in step by step techniques for decision making)

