##### Sample size

The sample-size calculation is based on change in RDQ at 3 months after onset of LBP. It is recommended that a change of 2 to 3 points on the RDQ should be considered the minimum clinically important change [48]. To allow for the cluster randomisation by PHCC, we assume an intraclass correlation coefficient of 0.1 [49] and a minimum average number of individuals sampled per PHCC of 25. In order to detect a difference of 2.5 points between the two intervention arms with a standard deviation of 5.7 [48,50], an alpha error of 0.05, a beta error of 0.10, and a 20% dropout rate, a sample size of 932 subjects was required, 466 subjects per intervention arm. Therefore, the total number of PHCCs is 38 (19 in each group).

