##### Statistical Analysis

The effectiveness of the intervention will be analysed in accordance with CONSORT guidelines, extended to a cluster randomised trial. The analysis will be carried out according to the intention-to-treat principle. Cost, outcomes and use of resources will be reported as mean values with standard deviations for each intervention arm. Comparisons will be done between arms on characteristics of the study population. Mean differences between groups in cost, outcomes and resources, and 95% confidence intervals were calculated. If cost data do not conform to the assumptions for standard statistical tests, the non-parametric bootstrap method will be performed [51].

To address potential biases due to incomplete follow-up, we will analyse patients with complete data at all time points and those with data at any time point, using the multiple imputation approaches to replace missing values. Bias due to non-response will be assessed at each follow-up.

The temporal horizon of the study is 3 months because this is the time of change to a chronic stage and 12 months to evaluate the outcomes at long term.

The discount rate will be 3% [52] that is closest to the actual discount rate.

To establish an important change in individuals, we will contrast the distributions of changes in all the questionnaires and in each assessment, in individuals who change to chronic state and those who do not [48]. We will do the same between those individuals who return to work and those who do not. We will compare individual change scores to the standard error of measurement (SEM).

To detect changes in groups, the intervention effect will be calculated through the effect size for each questionnaire and at each assessment. Effect size will be calculated following the method of Kazis et al [53].

We will evaluate responsiveness of each scale by standardized response mean (SRM) [54] and receiver-operating characteristic method (ROC curve). Since the unit of randomisation is the PHCC, we will use a regression analysis of individual level data using methods for clustered data [55].

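### Follow-up visits, including the 3-month RDQ that sizes the trial, are timed from onset of LBP although patients may enrol up to 12 weeks after onset, so time from baseline to that visit runs from about 7 to 76 days

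*Protocol article*

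**What the plan says.** Four parts of the protocol article bear on this point.

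- **Data collection and information sources** sets the visit clock: "They will be assessed at the first visit to the PHCC and at 3 months, 6 months, and 12 months after the onset of LBP".
- **Sample size** uses the same clock: "The sample-size calculation is based on change in RDQ at 3 months after onset of LBP". The onset anchor therefore appears twice.
- **Study population** admits a patient whose current episode "lasts between 15 days and 12 weeks". It also asks for at least 12 months' availability, without saying from when.
- **Intervention group** describes the sessions: "The programme consists of 2 sessions of 4 hours duration each and 1 session of 2 hours duration". On group size it says "Each group includes up to 12 participants". One psychologist and one physiotherapist cover all centres.

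The text after Table 4 lists the visits at 3, 6 and 12 months with no anchor. Statistical Analysis explains the first horizon: "The temporal horizon of the study is 3 months because this is the time of change to a chronic stage". Nothing in the article re-anchors the visits to enrolment, sets a minimum interval between the sessions and the 3-month visit, or says when sessions start or how far apart they are.

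**The concern.** The clock that defines the outcome starts before the patient enters the trial, by an amount that varies between patients. A patient enrolled near the end of the window has a baseline RDQ and a 3-month RDQ about a week apart, while one enrolled at the start has more than ten weeks between them. Both count equally in the contrast that sizes the trial, and intention-to-treat rightly keeps both in.

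Two things are at stake. First, intervention patients assessed before their sessions are complete pull the 3-month difference towards zero. Second, cost-effectiveness and cost-utility are the article's main outputs, and its Discussion speaks of a one-year horizon. On the onset clock, no patient has a full year of questionnaire-based utilities after enrolment, and the length observed differs from patient to patient.

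**Working it through.** **Step 1. Reproduce the sample size.** The inputs come from Sample size: "In order to detect a difference of 2.5 points between the two intervention arms with a standard deviation of 5.7", with "an alpha error of 0.05, a beta error of 0.10, and a 20% dropout rate", ICC 0.1 and 25 patients per centre. Alpha is taken as two-sided, which reproduces the stated figure.

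- Unclustered n per arm = 2 × [5.7 × (1.960 + 1.2816) / 2.5]² = 109.2, or 110 rounded up.
- Design effect = 1 + (25 − 1) × 0.1 = 3.4, giving 371 to 374 per arm.
- Dropout: dividing by 0.80 gives 465 to 468 per arm, or about 929 to 935 in total. The article states 932, so the figure is reproduced.
- Effective n per arm at 466 = 466 × 0.80 / 3.4 = 109.6. Standard error of the difference = 5.7 × √(2 / 109.6) = 0.770. Power at 2.5 points = Φ(2.5 / 0.770 − 1.96) = 90%.

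The sample-size arithmetic is not in dispute.

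**Step 2. Time from enrolment to each visit.** Take 3 months as 91 days, 12 months as 365 days and 12 weeks as 84 days.

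| Enrolled at | To 3-month visit | To 12-month visit |
|---|---|---|
| Day 15 | 91 − 15 = 76 days | 365 − 15 = 350 days (0.96 year) |
| Day 84 | 91 − 84 = 7 days | 365 − 84 = 281 days (0.77 year) |

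Counting 3 months as 90 to 92 days changes the first column to 75–77 and 6–8 days. The spread at every visit is 84 − 15 = 69 days, about 10 weeks. This step uses only the article's own rules.

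**Step 3. Is delivery within a week likely for late entrants?** The article does not say. With 466 intervention patients and at most 12 per group, at least 39 groups are needed (466 / 12 = 38.8). Over 19 centres, with about 25 patients each, that is two to three groups per centre. All share one psychologist and one physiotherapist. Completing three sessions within about 7 days of a given patient's enrolment looks unlikely as a rule, but this is an inference.

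**Step 4. Illustration of dilution.** This rests on three assumptions that are not in the article: enrolment spread evenly over days 15 to 84, a 2.5-point effect once delivery is complete, and no effect before. If delivery takes T days from enrolment, the share f assessed too early is (T − 7) / 69. Power is Φ(2.5 × (1 − f) / 0.770 − 1.96).

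| T (days) | f, rounded | Expected difference | Power |
|---|---|---|---|
| 7 or less | 0% | 2.50 | 90% |
| 14 | 7/69 ≈ 10% | 2.25 | 83% |
| 21 | 14/69 ≈ 20% | 2.00 | 74% |
| 28 | 21/69 ≈ 30% | 1.75 | 62% |

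Fewer late entrants, or partial benefit before the sessions end, would make the loss smaller. An enrolment pattern weighted towards late entry would make it larger.

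**The case against.** The strongest defence is that the onset clock was chosen for a reason: three months marks the passage to chronic LBP, and an enrolment clock would compare patients at different ages of the episode. That justifies onset timing for classifying chronicity. It does not justify measuring treatment effect, costs and QALYs on a clock that may leave about a week after baseline.

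The other objections limit how far the point can be taken. A reader might infer any of the following, and the article supports none of them.

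- **That late entrants cannot receive the sessions before the visit.** No session calendar is given, and the article refers to a separate effectiveness protocol, not shown, for more detail on the intervention. They may be assessed before completion; more than that is not established.
- **That the stated 90% power is lost.** The 2.5 points are justified by the minimum clinically important change, not as the effect expected after full exposure. Power for a 2.5-point difference at that visit is still 90%. The share of late entrants is unknown, and intervention patients also receive a booklet whose timing is not tied to the sessions.
- **That costs are observed for only 281 to 350 days.** Table 4 compares self-reported health care and sick leave with electronic records, so some use outside the visit window may be recoverable. Items that are self-reported only, such as presenteeism, home help and additional therapies, lack that check.
- **That QALYs will be computed on nominal intervals.** The article says utilities are adjusted for time and leaves the method open.
- **That follow-up length differs by arm.** GPs and nurses know their centre's allocation, so this is possible, but nothing shows it.

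**Conclusion.** The point holds as a conflict between the entry window and the visit anchor. From the stated rules alone, time from baseline to the 3-month visit varies from about 7 to 76 days, and the 12-month visit comes about 281 to 350 days after enrolment. For questionnaire-based utilities this means a post-enrolment period under one year that differs by about 10 weeks between patients. Using actual dates would describe that period correctly but would not supply utilities after the last visit.

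Dilution of the 3-month contrast is plausible but its size is unknown. The range from 90% down to about 62% rests on the assumptions in the working and should not be read as an estimate for this trial.

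**What to change.** **Visit timing.** Reconcile Study population, Data collection and Sample size. For patients not yet assessed, time the treatment-effect, cost and QALY assessments from the enrolment visit, and define the 3- and 12-month horizons from that date.

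**Analysis, all patients.** Record days from onset to enrolment and include it as a covariate. Use actual days since baseline in the repeated-measures model, in the QALY area under the curve and in cost accrual.

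**Chronicity.** Keep onset timing for classifying chronic LBP, using episode dates from interview and records, since a visit may no longer fall at three months from onset.

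**Cost.** A protocol amendment that moves each remaining visit later by the patient's own onset-to-enrolment time (15 days to 12 weeks), with no added patients or visits. The downside is that recruitment is under way, so patients already assessed stay on the onset clock. Two visit clocks would then coexist, and the analysis must handle them through actual elapsed time. If re-anchoring is judged too disruptive, the analysis changes alone are still worth making.
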